## 10. STATISTICS

### 10.1. Sample size

The total sample size of this trial will be 261 with 60 participants in ChAdOx1 nCoV-19 groups and 15 in each of the Meningococcal B vaccine groups for Groups 1 and 2. With a sample size of 60 participants, the probability of observing at least one participant with an adverse event will be more than 90%, if the underlying incident rate is 5%. The analysis for primary endpoints will be descriptive and there has been no formal power calculation to determine the sample size of the trial. The numbers have been therefore chosen based on practical constraints.

Following the updated safety guidance from the JCVI on 8th April 2021 [39], no more participants have been recruited. All the participant aged 6-11 years who randomised to group3 (boosted at 28 days) will be boosted at 112 days. The planned sample size of 75 has been achieved in Groups 1 and 2, and recruitment in Groups 3 and 4 stands at 55 and 56 respectively. As Groups 3 and 4 will both be boosted at D112 post prime, the two groups will be combined for all the safety and immunogenicity analysis. Therefore, the analysis of the younger age cohort will have increased power.

#### Description of Statistical Methods

A fully detailed statistical analysis plan will be developed and signed by the chief investigator prior to any data analysis being conducted. In brief, the analysis will incorporate the following;

##### 10.1.1. Safety and reactogenicity

All SAEs will be presented for each group using descriptive analyses, including any evidence of disease enhancement, hospital admissions and cases of suspected PIMS-TS.

Counts and percentages of each local and systemic solicited adverse reaction from diary cards, and all unsolicited AEs, and SAEs of special interest will be presented for each group.

##### 10.1.2. Immunogenicity

Highly skewed ELISA and neutralising antibody data will be log-transformed prior to analysis. The geometric mean concentration (GMC) and associated 95% confidence interval (CI) will be summarised by computing the anti-log of the mean of the log-transformed data.

The GMCs and CIs at day 28 post prime and boost, and the proportion of participants seroconverting (defined as a greater than a four-fold rise) from day 0 to day 28 post boost will be computed.

Spike-specific T cell responses (ELISPOT) will be presented as means and confidence intervals, or medians and interquartile ranges if non-normally distributed at all post vaccination time points.

Comparisons of continuous immunogenicity data between groups or different time points will be made using a Mann Whitney U test because the low titres below detection threshold are expected, which will cause a non-normal distribution. Comparison of seroconversion rates will be conducted using a Chi-squared test.

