| 2                                  | 75                                                                                                                                                                                                                                                                                                                                                                                                                                                                                                                                                                                           |                                                       | ChAdOx1 nCoV-19 5.0 x10  vp (N=60) OR MenB (N=15) with homologous boost at D112 |       |   |     |          |   |    |             |                                                                                             |   |    |                                                                                              |   |    |            |                                                                                              |   |    |
| 3                                  | 56                                                                                                                                                                                                                                                                                                                                                                                                                                                                                                                                                                                           | 6-11 years                                            | ChAdOx1 nCoV-19 5.0 x10  vp (N=90) OR MenB (N=21) with homologous boost at D112 |       |   |     |          |   |    |             |                                                                                             |   |    |                                                                                              |   |    |            |                                                                                              |   |    |

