| Primary
To assess the safety, tolerability and reactogenicity profile of a prime-boost regimen (with an interval between prime and boost of 28 OR 112 days in 12-17 year olds, and interval of 112 days in 6-11 year olds) of the candidate vaccine ChAdOx1 nCoV-19 ( $5.0 \times 10^{10}$ vp / $5.0 \times 10^{10}$ vp) in children aged 6-17 years. | a) occurrence of solicited local reactogenicity signs and symptoms for 7 days following vaccination;
b) occurrence of solicited systemic reactogenicity signs and symptoms for 7 days following vaccination;
c) occurrence of unsolicited adverse events (AEs) for 28 days following vaccination;
d) occurrence of SAEs and disease enhancement episodes
e) occurrence of abnormal laboratory findings (Grade 3 and above) | a)-c) as stated, d) throughout the study, e) D2 and D7 post-boost blood tests (safety bloods) |
| Secondary
To assess cellular and humoral immunogenicity of ChAdOx1 nCoV-19 ( $5.0 \times 10^{10}$ vp / $5.0 \times 10^{10}$ vp) given as homologous prime boost (at 28 and 112 days post prime in 12-17 year olds, and 112 days post prime in children aged 6-11 years)                                                                               | a) Quantify antibodies against SARS-CoV-2 spike protein (seroconversion rates)
b) Virus neutralising antibody (NAb) assays against live and/or pseudotype SARS-CoV-2 virus
c) Interferon-gamma (IFN- $\gamma$ ) enzyme-linked immunospot (ELISpot) responses to SARS-CoV-2 spike protein
d) cell analysis by flow cytometry assays                                                                                            | Blood samples drawn at D0, D28, D56, , D84, D112, D140, D182 and 364                          |

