### **10.2. Analysis population**

All participants received at least one dose of study vaccines will be included in the analysis of safety and will be analysed according to vaccine received.

The immunogenicity analyses will include participants who are seronegative to the spike protein at baseline and received both prime and boost vaccine. Sensitivity analyses of immunogenicity data will be conducted including all vaccinated participants regardless of seropositivity status and protocol deviations.

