### **10.4. The Level of Statistical Significance**

There will be no statistical significance testing for primary endpoints of safety. For secondary endpoints of immunogenicity, the level of significant will be two-sided 0.05.

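### Section 10.1.2 names an unpaired rank test for time-point comparisons that are mostly repeated measures on the same children, so p-values are conservative and modest changes such as waning are easily missed

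*Protocol*

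**What the plan says.** Protocol section 10.1.2 (Immunogenicity) names one test for two kinds of comparison: "Comparisons of continuous immunogenicity data between groups or different time points will be made using a Mann Whitney U test". The reason follows in the same sentence: "because the low titres below detection threshold are expected, which will cause a non-normal distribution". Formal testing is intended. Section 10.4 says "For secondary endpoints of immunogenicity, the level of significant will be two-sided 0.05".

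The time points are serial bloods. The secondary endpoints in section 4 list "Blood samples drawn at D0, D28, D56, , D84, D112, D140, D182 and 364", and each group follows part of that list (Tables 5a to 5d):

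- Group 1: D0, D28, D56, D182 and D364.
- Groups 2 and 4: D0, D84, D112, D140 and D364.
- Group 3: D0, D28, D84 and D112, after which a footnote to the schedule tables allocates each child to either V5 (D140) or V6 (D364).

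The main immunogenicity population is set out in section 10.2: "The immunogenicity analyses will include participants who are seronegative to the spike protein at baseline and received both prime and boost vaccine". No paired method is named anywhere in the protocol.

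**The concern.** The Mann-Whitney test compares two sets of values as if they came from different people. Within a group, most time-point comparisons set a child's value against the same child's value on another day. If children who are high on one day tend to be high on the other, the difference between the two days varies less than the test supposes. The test then uses too large a standard error and rejects too rarely.

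The stated justification concerns the shape of the distribution. It explains why a t-test might be avoided, but the signed-rank test and the sign test are also rank or sign methods and respect the pairing.

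What is at stake is the reading of a non-significant result. A gradual fall in antibody, for example between D84 and D112 before the boost, could be reported as no significant change because the within-child information was set aside.

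**Working it through.** **The plan's own figure.** Section 10.1 gives one design figure: "With a sample size of 60 participants, the probability of observing at least one participant with an adverse event will be more than 90" per cent "if the underlying incident rate is 5" per cent. The check is 1 − 0.95^60 = 0.954, so it reproduces. It concerns adverse events. The protocol states no power, effect size, SD or within-child correlation for immunogenicity.

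**Inputs.**
- Two-sided alpha 0.05 (section 10.4).
- n = 60 per ChAdOx1 arm in Groups 1 and 2 (section 10.1). For Groups 3 and 4, which section 10.1 pools, n = 90: "vp (N=90) OR MenB (N=21) with homologous boost at D112" (synopsis).
- Spread, back-calculated from the 95% confidence intervals in Table 1b: SD of ln titre = √N × ln(upper/lower) / (2t), with t the 97.5% point on N − 1 degrees of freedom. After dose 1 at under 6 weeks: √479 × ln(9,676.9/7,883.1) / (2 × 1.965) = 1.14, or 0.50 in log10 units. After dose 2 at 9–11 weeks: 0.71, or 0.31. Post-dose cells therefore span about 0.31 to 0.50 in log10 units. The simulations use an ln SD of 1.1 at both times (1.1/2.303 = 0.48 in log10), close to the post-dose-1 values.
- Adult boost size, Table 1b: 22,222.73/8,734.08 = 2.5-fold (under 6 weeks) and 63,181.59/8,618.17 = 7.3-fold (over 12 weeks).
- Within-child correlation ρ of log titres: assumed, range 0.3 to 0.7.

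**Type I error.** When the two time points have the same distribution, pairing multiplies the variance of the Mann-Whitney statistic by about 1 − ρ_S, where ρ_S = (6/π) arcsin(ρ/2) is the Spearman correlation. The true size is then 2 × [1 − Φ(1.96/√(1 − ρ_S))].

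| ρ | ρ_S | 1.96/√(1 − ρ_S) | Size by formula | Simulated, n = 60 | Simulated, n = 90 |
|---|---|---|---|---|---|
| 0.3 | 0.288 | 2.32 | 2.0% | 2.1% | 1.9% |
| 0.5 | 0.483 | 2.72 | 0.6% | 0.6% | 0.6% |
| 0.7 | 0.683 | 3.48 | 0.05% | 0.1% | 0.05% |

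These simulations used 10,000 runs. Shorter runs with other SDs gave 2.4% and 3.0% at ρ = 0.3, hence about 2–3%. The signed-rank test stayed between 4.5% and 5.2% throughout.

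**Power** (bivariate normal ln titres, SD 1.1, 2,000 runs; Mann-Whitney v signed-rank). A fall has the same power as a rise of the same size.

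| Change | n | ρ = 0.3 | ρ = 0.5 | ρ = 0.7 |
|---|---|---|---|---|
| 1.25-fold | 60 | 15% v 26% | 10% v 31% | 6% v 49% |
| 1.5-fold | 60 | 49% v 63% | 51% v 79% | 50% v 94% |
| 2-fold | 60 | 95% v 98% | 97% v 99.8% | 99% v 100% |
| 1.5-fold | 90 | 69% v 81% | 73% v 93% | 79% v 99% |

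**Boosts of adult size.** With the Table 1b SDs and n = 60, a 2.5-fold rise is detected with 99.6% to 100% power by either test at ρ = 0, 0.5 and 0.7. A 7.3-fold rise is detected with 100% by either.

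**The case against.** The strongest defence is that the error is on the safe side and touches little. With positive correlation the test rejects too rarely, so it does not create false claims of boosting or waning. The primary safety analysis is descriptive and untested. The geometric means with their intervals, the seroconversion rates and the comparisons between groups do not depend on this choice. All of that stands, and it sets the severity.

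A second defence is that a full statistical analysis plan is promised before analysis. This does not remove the point. The protocol says the analysis will incorporate the methods it lists, and it then names the test. A plan that follows it inherits the unpaired test, and one that corrects it departs from the protocol.

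Three stronger readings are tempting, and the documents do not support them:

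- A reader might infer that the p-values produce false positives. That would need negative within-child correlation (at −0.3 the size would be 8.5%), which is not the usual case for repeated titres.
- A reader might infer that most of the power to detect boosting is lost. At the adult boost sizes in Table 1b both tests have at least 99.6% power. More than half the power is lost only for changes of about 1.3-fold or less at correlations of about 0.5 or more.
- A reader might infer that every time-point comparison is paired. In Group 3 the footnote allocates a child to D140 or D364, so on that wording those two samples come from different children. Comparisons of different days across different groups are also independent.

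**Conclusion.** The protocol fixes an unpaired test for comparisons that are mostly paired, for a reason that does not bear on pairing. The p-values for those comparisons are miscalibrated in the conservative direction, and the practical loss falls on modest changes. At 1.5-fold with 60 children, signed-rank power is higher by 14 points at correlation 0.3 (63 − 49) and by 44 points at 0.7 (93.5% − 49.6% before rounding).

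The size of the loss rests on assumptions. The documents give neither the within-child correlation nor an expected amount of waning, so it can only be stated as a range. The simulations take normal log titres with no values below detection. They also use the full arm sizes, whereas the analysed numbers will be smaller if children are seropositive at baseline or decline the booster (section 6.3.6 allows for this).

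Only secondary within-group comparisons are affected. This should be fixed before analysis; it does not threaten the trial's main conclusions.

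**What to change.** In section 10.1.2, and in the statistical analysis plan to match:

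- Keep the Mann-Whitney test for comparisons between independent groups.
- For comparisons between time points in the same participants, use the Wilcoxon signed-rank test on within-participant log differences, or the sign test if many pairs are below detection. Report the geometric mean fold change with its 95% confidence interval.
- Where children are sampled at only one of the two time points (Group 3, D140 or D364), use an unpaired comparison, or a mixed model on log titres with a stated method for values below detection. When Groups 3 and 4 are pooled, D140 against D364 mixes paired children from Group 4 with unpaired children from Group 3. The mixed model is the natural choice there, because a signed-rank test on complete pairs would drop Group 3.

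The cost is a sentence or two of text and no new data. Under the signed-rank test only children with both samples contribute, so the number of pairs should be reported with each comparison.

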**Table 1b) SARS CoV-2 S-binding antibody response to ChAdOx1 nCoV-19**

| Dose interval | Baseline GMT (95% CI)      | 28 days after dose 1 (95% CI)        | 28 days after dose 2 (95% CI)           |
|---------------|----------------------------|--------------------------------------|-----------------------------------------|
| <6 weeks      | (N=481) 60.51 (54.1; 67.7) | N=479) 8,734.08 (7,883.1; 9,676.9)   | (N=443) 22,222.73 (20,360.50; 24,255.3) |
| 6-8 weeks     | (N=137) 58.02 (46.3; 72.6) | (N=99) 7,295.54 (5,857.4; 9,086.7)   | (N=116) 24,363.10 (20,088.5; 29,547.3)  |
| 9-11 weeks    | (N=110) 48.79 (39.6; 60.1) | (N=87) 7,492.98 (5,885.1; 9,540.2)   | (N=106) 34,754.10 (30,287.2; 39,879.8)  |
| >12 weeks     | (N=154) 52.98 (44.4; 63.2) | (N=152) 8,618.17 (7,195.4; 10,322.3) | (N=154) 63,181.59 (55,180.1; 72,343.4)  |

GMT: geometric mean titre, evaluated using multiplex immunoassay

COV006 will be the first time that ChAdOx1 nCoV-19 is administered to participants under the age of 18. However, ChAd vectored vaccines have previously been administered to over 400 children and adolescents aged 5-17 years of age [28] as well as children of younger ages, with acceptable safety and tolerability profiles; these children took part in clinical studies conducted by or in partnership with the University of Oxford in the UK and overseas (Table 2). ChAd vectored vaccines were given at doses ranging from  $2.5 \times 10^{10}$  to  $1.0 \times 10^{11}$  vp and no serious adverse reactions related to the vaccine were reported (Table 2).

Following the initial phase of recruitment of 6-11 year olds in this trial, and a review of the D7 diary card data in this population, the DSMB noted that the reactogenicity profile of the younger cohort might be higher than in the older age group and therefore safety bloods were warranted in a subset of this cohort.

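### Between ChAdOx1 groups the four-fold seroconversion rate is probably at its ceiling, so the planned chi-squared test would usually be undefined or uninformative

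*Protocol*

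**What the plan says.** Protocol section 4 lists the first secondary outcome as "a) Quantify antibodies against SARS-CoV-2 spike protein (seroconversion rates"). Section 10.1.2 says that "the proportion of participants seroconverting (defined as a greater than a four-fold rise) from day 0 to day 28 post boost will be computed", and then fixes the test: "Comparison of seroconversion rates will be conducted using a Chi-squared test". It does not say which groups are compared and gives no alternative for sparse tables. The subgroup list that follows (numbered 8.1.3) adds comparisons by sex, age band and baseline serostatus. Section 10.4 says that for immunogenicity "the level of significant will be two-sided 0.05".

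The same section 10.1.2 also plans geometric mean concentrations with 95% confidence intervals at day 28 post prime and post boost, and says: "Comparisons of continuous immunogenicity data between groups or different time points will be made using a Mann Whitney U test".

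Section 10.2 restricts the main immunogenicity analysis to children who are spike-seronegative at baseline and received both doses. Section 10.1 gives 60 ChAdOx1 recipients in each of Groups 1 and 2, and has Groups 3 and 4 both boosted at D112 and pooled.

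**The concern.** A test of two proportions needs some participants who fail the criterion. Table 1b in section 3.2 shows adult geometric means rising several hundred-fold by 28 days after dose 2, against a threshold of four. If children respond similarly, nearly every vaccinated child passes at either interval. When both groups reach 100%, the chi-squared statistic has no value. When one or two children fail, the expected counts are too small for the approximation.

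Group 1 v Group 2 is the only randomised schedule contrast left after the amendments. A missing or non-significant p-value for a listed secondary measure could be read as evidence that the two schedules are equally immunogenic, which it would not be.

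**Working it through.** **The plan's own figure.** The protocol gives no expected rate or power for seroconversion. Its only design figure is a more than 90% chance of at least one adverse event in 60 participants at a 5% rate. This reproduces: 1 − 0.95^60 = 95.4%.

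**Inputs (Table 1b, adults, multiplex assay).**
- Interval <6 weeks: baseline 60.51 (54.1 to 67.7), N=481. After dose 2: "N=443) 22,222.73 (20,360.50; 24,255.3").
- Interval >12 weeks: baseline 52.98 (44.4 to 63.2), N=154. After dose 2: "N=154) 63,181.59 (55,180.1; 72,343.4").

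**Step 1: fold rises.** 22,222.73/60.51 = 367. 63,181.59/52.98 = 1,193.

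**Step 2: spread.** SD(ln titre) = ln(upper/lower)/(2t) × √N, where t is the 97.5% t quantile on N − 1 degrees of freedom.
- <6 weeks: 1.252 at baseline, 0.937 post boost.
- >12 weeks: 1.109 at baseline, 0.851 post boost.

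The within-person correlation is not given. I assume 0 and vary it below. The SD of the log fold-rise is then √(1.252² + 0.937²) = 1.564 and √(1.109² + 0.851²) = 1.398.

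**Step 3: proportion above four-fold, assuming log-normal titres.** P = Φ((ln ratio − ln 4)/SD).
- <6 weeks: Φ((5.906 − 1.386)/1.564) = Φ(2.89) = 99.81%.
- >12 weeks: Φ((7.084 − 1.386)/1.398) = Φ(4.08) = 99.998%.

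With 1.96 in place of the t quantile these become 99.80% and 99.997%. The same formula on the post-dose-1 titres (144-fold and 163-fold rises) gives about 98.3% and 99.0%. Most of the ceiling is therefore reached before any boost.

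**Step 4: the chi-squared test at 60 v 60.** The probability that nobody fails in either group is 0.99808^60 × 0.99998^60 ≈ 0.89. With equal arms the smallest expected count is half the total number of non-converters, so it stays below 5 unless at least 10 of 120 fail. Enumerating all binomial tables (uncorrected chi-squared, two-sided 0.05):

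| Assumption | Rates | P(undefined) | P(p<0.05) |
|---|---|---|---|
| Table 1b, correlation 0 | 99.81% v 99.998% | 0.89 | <0.0001 |
| Correlation −0.3 | 99.46% v 99.98% | 0.71 | 0.0003 |
| Correlation 0.5 | 99.997% v ~100% | 0.998 | ~0 |
| SD × 1.25 | 98.96% v 99.94% | 0.52 | 0.003 |
| SD × 1.5 | 97.30% v 99.67% | 0.16 | 0.065 |

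In every row, nearly all the remaining tables have a smallest expected count below 5.

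**Step 5: false positives.** With equal true rates at 60 v 60, the uncorrected chi-squared rejects with probability 0.00001, 0.003, 0.019, 0.035 and 0.046 at non-conversion of 0.2%, 1%, 2%, 3% and 5%. Over the same rates the maximum is 0.052 at 48 v 48 and 0.055 at 90 v 120 (the age comparison).

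**Step 6: comparison with MenB.** If 60/60 and 0/15 convert, chi-squared is 75.0 (p about 5 × 10⁻¹⁸). The smallest expected count is 3.0, but the conclusion is not in doubt.

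**Step 7: the titre comparison.** The adult ratio between schedules is 63,181.59/22,222.73 = 2.84, so the log difference is 1.045. With SD 0.94 and 60 per arm the standard error is 0.94 × √(2/60) = 0.172. The difference is 6.1 standard errors, and power exceeds 99.9%. At 30 per arm it is about 99%.

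**The case against.** A reader might infer four stronger things, none of which the document supports.

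- *The chi-squared test is mostly undefined in this trial.* Section 10.1.2 names no comparators, and the trial has a MenB control arm against which the test is computable and decisive. The problem is confined to comparisons between ChAdOx1 groups.
- *The test gives false positives because expected counts are small.* Step 5 shows rejection near or below 0.05. Chi-squared does reject more often than Fisher's test when rates truly differ (5.9% v 0.5% at 97% v 99%), but that is power and not excess error.
- *The schedule question is lost.* The geometric means and the Mann-Whitney comparison are planned in the same section and would detect a difference of the adult size. The protocol nowhere rests the schedule conclusion on seroconversion.
- *The protocol shows that children will saturate.* Table 1b is adult multiplex data, and the protocol says this is the vaccine's first use under 18. Section 10.1.2 concerns ELISA and neutralising antibody and expects some values below detection, which strains a log-normal model. No fold-rise data are given for neutralising antibody.

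It can also be said that sparse-table rules belong in the statistical analysis plan, which the protocol promises and which is not at hand. This stands for the finer detail. It does not remove the point, because the protocol itself names the test. The synopsis also omits seroconversion from the wording of this outcome, which limits the weight it carries.

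**Conclusion.** The point holds for comparisons between ChAdOx1 groups only. On the protocol's adult titres the endpoint is at its ceiling. The D28 v D112 chi-squared test at 60 v 60 would return no statistic with probability about 0.89, and its power is effectively nil. The size of the problem depends on log-normality, on the unstated correlation, and on children resembling adults. A spread 1.25 or 1.5 times larger lowers the probability of an undefined test to 0.52 or 0.16, but power stays at 0.3% or 6.5%. The conclusion that the test cannot separate the schedules is therefore more robust than the exact chance of an undefined result. Restricting the main analysis to seronegative, two-dose children should push rates closer to 100%. The consequence is an uninformative secondary test that could be misread, not a lost or biased conclusion.

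**What to change.** In section 10.1.2:

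1. Report seroconversion per group with an exact (Clopper-Pearson) 95% confidence interval. For 60/60 the lower limit is 0.025^(1/60) = 94.0%.
2. Between ChAdOx1 groups, replace the chi-squared p-value with a score or exact interval for the difference in proportions. This can be computed even at 100% v 100%.
3. Where a test is kept and any expected count is below 5, use an exact test.
4. State that the D28 v D112 comparison rests on the titres at day 28 post boost, and that similar seroconversion rates will not be read as equal immunogenicity.

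The cost is a few sentences and no new data. The downside is that Fisher's test is more conservative than chi-squared and returns p = 1 when both groups reach 100%. The interval should therefore be the main summary, with the test secondary to it.
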